**4-6-2　Protocol Treatment**

　Study Design

Single-arm, open-label, uncontrolled, single-comparison study

Treatment with research equipment

Efficacy and safety assessment

Obtaining written consent

Eligibility Verification and Registration

<Protocol Treatment>

The position of the patient during the protocol is the sitting position, and the following order is used.

[At the time of obtaining consent]

After obtaining consent, a questionnaire (background investigation) will be conducted.

[Before treatment]

1. After resting for 5 minutes, vital signs will be measured.
2. The research subject will fill out the questionnaire (before the procedure).
3. Observe the skin at the treatment site.
4. Measurements will be made in the following order: muscle ultrasonography of both shoulders, surface electromyography, thermography, and pressure pain threshold. At the end of the electromyography, continuous blood pressure monitoring and continuous measurement of heart rate variability are performed.
5. The results of the examination are confirmed, and the treating side is decided.

(Criteria for determining the treating side)

The side with the lower pressure sore meter reading is the treatment side.

[Treatment] 1.

1. irradiate LED light acupuncture needles to the shoulder well (a common acupuncture point for stiff shoulders).

（Irradiate the silicon rubber part of the LED acupuncture needle directly onto the skin of the shoulder well for 30 seconds per irradiation. After irradiation, check the condition of the skin, and continue irradiation after 3 seconds until the skin shows a reddish change to the naked eye from before irradiation. Repeat irradiation up to 6 times.

[Immediately after the treatment]

1. Immediately after the LED acupuncture irradiation, skin observation, thermography, and pressure pain threshold (on the treated side only) should be performed. (After the measurement, cover the treated area with a bath towel.
2. The research subject will fill out the questionnaire (immediately after the treatment).

[15 minutes after the treatment].

1. 15 minutes after the end of irradiation, skin observation, thermography, pressure pain threshold (on the treated side only), muscle ultrasonography, and surface electromyography are measured in this order. The Finapres NOVA will be removed when the tenderness meter measurement is completed.
2. The research subject will fill out a questionnaire (15 minutes after the treatment).

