3. After 5 minutes of rest, vital signs will be measured.

[Post-procedure observation: 7 ± 2 days after the procedure.

Skin observation will be performed to evaluate safety.

<Examination and evaluation methods

1. Vital signs: Blood pressure and pulse are measured using a sphygmomanometer.
2. Tension and tenderness meter: Measure the circumference of the shoulder well within 10 mm in diameter twice, and calculate the average value.
3. Thermography:
   1. Measure the body surface temperature of the subject's entire body.
   2. Measure body surface temperature within a range of about 10 cm centered on the area irradiated with LEDs.
4. Continuous blood pressure, heart rate, heart rate variability, and BRS test: Measurements will be made using electrocardiogram electrodes and Finapres NOVA.
5. Surface electromyography: Weight-loading test is performed on the shoulder of the treatment site, and muscle fatigue caused by the loading is evaluated by surface electromyography.
   1. Perform the test in a sitting posture. (2) The subject's arms are placed on a desk at rest, and after a 15-second measurement at rest, a 2-minute measurement of (weight) loading is performed.
   2. The load is applied by holding a 2- to 3-kg weight on the treating side and holding it as follows The upper arm is held horizontally forward and the forearm is flexed 90 degrees vertically upward for 15 seconds, and then the forearm is held in extension for up to 2 minutes with the weight and measured. The arm of the non-treated side should be in a posture to support the upper body so that the muscle load on the trunk is excluded. The loading time is 2 minutes, but may be shortened if the subject does not tolerate the weight load or the maintenance of the posture. (When shortening the loading time, the change in EMG from the state of no muscle fatigue to the state of fatigue is measured, so there will be few problems in data collection.)
6. Measurement of the EMG load is performed on the shoulder on the side to be treated.

The measurement site should be the trapezius muscle (especially from the neck to the shoulder) and the deltoid muscle.

1. Muscle ultrasonography: Measurement is made simultaneously with the above surface EMG examination process.
   1. Echocardiography is performed on the trapezius muscles (especially from the neck to the shoulders) and deltoid muscles at rest and during loading.
   2. Avoid electrode positions for the above muscles when performing echo.

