   3. A comparison of echo intensity (luminance, muscle contraction, muscle thickness, etc.) of the muscles under weight lifting is performed.

<Observational Examination/Item>.

After obtaining consent, the background of the research subjects will be investigated.

- Study subject background: age, gender, medical history of cervical spine disease, a survey of medications used
- Vital signs: blood pressure, pulse (heart rate), heart rate variability (LF, HF, LF/HF), baroreflex sensitivity (BRS)
- Clinical findings: skin observation (presence of redness)
- Thermography: skin surface temperature of the whole body and the area to be treated
- Pressure pain threshold: measurement of the circumference of the shoulder well within 10 mm in diameter
- Surface electromyography: measurement of the amplitude and frequency of surface electromyograms generated from the trapezius (especially from the neck to the shoulder) and deltoid muscles over time to determine muscle fatigue associated with loading.
- Muscle ultrasonography: measurement of muscle echo changes (e.g., brightness) over time in the trapezius (especially from the neck to the shoulder) and deltoid muscles during loading.
- Questionnaire: (Background survey) Daily living situation, (Before treatment)
- (Before the treatment) Pain due to stiffness in the shoulders (VAS), evaluation of stiffness in the shoulders (VAS)
- (Immediately after the treatment) Pain due to stiff shoulders (VAS), evaluation of stiffness in the shoulders (VAS), evaluation of sensation during the treatment
- (15 minutes after treatment) Pain due to stiff shoulders (VAS), evaluation of stiffness in the shoulders (VAS), evaluation of sensation during treatment (VAS)
- Adverse event (skin burn)

＜Schedule＞

|  | **VISIT 1** | **VISIT 2** | | | | **VISIT　3** |
| --- | --- | --- | --- | --- | --- | --- |
|  |  | **Day of treatment** | | | | **7 ±2 days after treatment** |
|  |  | Before the treatment | **Treatment** | Immediately after the treatment | 15 minutes after treatment |  |
| Obtaining written consent | **○^＊1^** | |  |  |  |  |
| Background evaluation | **○^*1^** | |  |  |  |  |
| Treatment |  |  | **○** |  |  |  |
| Vital Signs Assessment |  | **○** |  |  | **○** |  |
| Continuous blood pressure heart rate measurement, heart rate variability, BRS test ^*２^ |  |  |  |  |  |  |
| pressure pain threshold |  | **○** |  | **○** | **○** |  |
| Thermography |  | **○** |  | **○** | **○** |  |

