**7.** **Evaluation of Efficacy**

**7-1. Efficacy Endpoints**

Primary endpoint: subjective symptoms (VAS)

Secondary endpoints: changes in skin temperature, baroreflex sensitivity (BRS), autonomic nervous system function (heart rate variability)

Exploratory endpoints: muscle properties observed by ultrasonography (luminance, muscle contraction, muscle thickness, etc.), changes in surface electromyography (amplitude, frequency, etc.)

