**9-1-3** **Analysis of secondary endpoints**

- On the treated side, the pre-, immediate post-, and 15-minute post-treatment tenderness meter and skin temperature measurements over time will be analyzed using one-way repeated measure ANOVA or Friedman's test.
- ~~One-way repeated measure ANOVA or Friedman's test will be used to analyze the pressure pain threshold, skin temperature, and subjective symptoms (VAS) measurements over time before, immediately after, and 15 minutes after the treatment on the non-treatment side.~~
- ~~Differences between the treated and non-treated sides of the pressure pain threshold, skin temperature readings, and subjective symptoms (VAS) over time before, immediately after, and 15 minutes after the treatment will be analyzed using two-way repeated measure ANOVA or Friedman's test.~~
- Heart rate variability frequency analysis will be performed to compare changes in the low frequency (LF) range and the power ratio of the low-frequency range to the high-frequency range (LF/HF) from before to 15 minutes after treatment. Average values will be taken before (5 minutes), ~~during (up to 3 minutes)~~, immediately after (5 minutes), and 15 minutes after (5 minutes) the procedure and analyzed using One-way repeated measures ANOVA or Friedman's test.
- Comparison of baroreceptor reflex sensitivity before, immediately after, and 15 minutes after the procedure

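### The towel placed over the treated area between the immediate and 15-minute thermograms is confounded with the device effect on skin temperature at 15 minutes

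*Protocol*

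**What the plan says.** Protocol 4-6-2 fixes the sequence. Before treatment, thermography follows muscle ultrasonography and surface electromyography (EMG). After irradiation come skin observation, thermography and the pressure pain threshold, and then the instruction "After the measurement, cover the treated area with a bath towel". The next thermogram is tied to the clock: "15 minutes after the end of irradiation, skin observation, thermography, pressure pain threshold (on the treated side only), muscle ultrasonography" and then surface EMG. The schedule table in the same section marks thermography at all three times.

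The region of interest is the covered skin: "Measure body surface temperature within a range of about 10 cm centered on the area irradiated with LEDs". A second, wider recording is also specified: "Measure the body surface temperature of the subject's entire body".

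Sections 4-1-2 and 7-1 list skin temperature as a secondary endpoint. Section 9-1-3 sets the analysis: "On the treated side, the pre-, immediate post-, and 15-minute post-treatment tenderness meter and skin temperature measurements over time will be analyzed", by one-way repeated-measures ANOVA or Friedman's test. The lines in 9-1-3 on the untreated side and on the difference between sides are struck through. Section 4-6-2 describes the study as having one arm and no control.

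**The concern.** A before-after comparison on one side can be read as a treatment effect only if the other conditions that act on the measurement are the same at each reading. Here one of them changes by instruction. The skin may lie under a towel for most of the 15 minutes before the third thermogram, while no cover is described before the first or second. Nothing states when the towel comes off or how long the skin is exposed before the image is taken.

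At stake is the interpretation of one time point of a secondary endpoint. Section 2-1 names skin temperature among the physiological tests on which a favourable effect is looked for, and the background cites dilation of small vessels and increased blood flow as the expected action. Of the two post-treatment readings, the 15-minute one is the later and speaks to whether any change lasts. It is also the one that the towel can disturb. The three-time test includes that reading, so a significant result from it has the same ambiguity.

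**Working it through.** **Which contrasts carry the towel**

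| Reading | Cover stated for the treated area | Device applied |
|---|---|---|
| Before | none | no |
| Immediately after | none (towel comes after this reading) | yes |
| 15 minutes after | towel since the immediate reading; removal time not stated | yes |

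Let D1 and D2 be the device effects at the immediate and 15-minute readings, and T the towel effect at 15 minutes.

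- Immediate minus before estimates D1. T does not enter.
- 15 minutes minus before estimates D2 + T. On the treated side alone, no second equation separates the two terms.
- The three-time test has the null hypothesis D1 = 0 and D2 + T = 0. It can reject when both device effects are zero.

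**How often that would happen (assumed illustration)**

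The plan has no figure to reproduce: section 9-3 says that the 10 subjects have no statistical basis, and no SD or towel effect is given. The inputs are therefore:

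- From the protocol: k = 3 times; n = 10 planned, with about 5 to 7 as the evaluable minimum (9-3); level 0.05 (9-4).
- Assumed: D1 = D2 = 0, independent normal residuals, and a towel shift of d within-subject residual SD at 15 minutes, with d from 0 to 2.

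For the repeated-measures ANOVA, F has k − 1 = 2 and (k − 1)(n − 1) = 18 degrees of freedom. One mean out of three shifted by d gives a noncentrality of λ = n × (2/3) × d². For n = 10 and d = 1, λ = 10 × 0.667 × 1 = 6.67. The critical value is 3.555, and the noncentral F gives a rejection probability of 0.556. Simulation of 20,000 trials per setting agrees (0.554) and also gives Friedman's test:

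| Towel shift d (n = 10) | ANOVA | Friedman | Before vs immediate (paired t) |
|---|---|---|---|
| 0 | 0.049 | 0.045 | 0.049 |
| 0.5 | 0.172 | 0.131 | 0.049 |
| 1.0 | 0.554 | 0.411 | 0.047 |
| 1.5 | 0.901 | 0.757 | 0.047 |
| 2.0 | 0.991 | 0.943 | 0.051 |

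With fewer evaluable subjects and d = 1, the ANOVA and Friedman figures are 0.375 and 0.293 at n = 7, and 0.256 and 0.179 at n = 5. The before-to-immediate contrast stays at about 5% throughout.

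**Whether the other shoulder alone would solve it**

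Suppose the treated-minus-untreated change at 15 minutes were tested with the untreated shoulder left uncovered. The difference of two changes has a variance of four residual variances, so the standardised shift is d/2. At n = 10 the simulation rejects in 0.291 of trials for d = 1 and 0.802 for d = 2. A side comparison without matched covering remains biased.

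**The case against.** Several points on the other side are sound.

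- **Size.** The percentages depend wholly on the assumed shift. A paired 15-minute-versus-baseline t-test at n = 10, with an assumed SD of change of 0.5 °C, rejects in only 0.059 of trials for a 0.05 °C towel effect and 0.088 for 0.1 °C. A small towel effect would do little harm. This stands. The confounding does not depend on the size, but the damage does.
- **Direction.** A reader might infer that the towel always favours the device, because cloth insulates. The documents do not support that for the net result. Baseline thermography follows surface EMG, in which a 2 to 3 kg weight is held for up to 2 minutes, whereas the 15-minute thermogram comes before the repeat EMG. Any warming from that exertion would raise the baseline and work the other way.
- **Extent of the cover.** A reader might also infer that only the treated shoulder is covered. The protocol orders cover for the treated area and is silent on the other shoulder and on clothing or cover before baseline. A bath towel may reach well beyond a field of about 10 cm. What can be said is that covering is unspecified elsewhere.
- **The untreated side as a control.** It is tempting to say that the opposite shoulder would cancel everything except the device. It would not. The EMG load is described for the treating side, so baseline may differ between sides. Section 2-1 cites sympathetic inhibition as a possible mechanism, and a systemic effect would be subtracted out with the control side.
- **Design.** The study is openly uncontrolled, and removal of the side analyses from 9-1-3 is not itself an error. Drift in room temperature and time spent sitting are general limits of any before-after study and do not arise from the towel.

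None of this removes the core point. The protocol itself introduces a change in measurement condition before one of the three readings, and the planned analysis cannot separate it from treatment.

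**Conclusion.** The point holds in a limited form. As written, any towel effect on skin temperature is confounded with the device effect in the 15-minute contrast and in the three-time test. The before-to-immediate contrast is free of it.

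The size and net direction of the towel effect cannot be taken from the documents. Under an assumed towel-only shift of 0.5 to 2 within-subject SD, with independent normal residuals, no device effect and 10 subjects, the planned tests would be significant in about 13% (Friedman, 0.5 SD) to 99% (ANOVA, 2 SD) of trials instead of 5%. Below that range the excess is smaller.

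The consequence is confined to one reading of a secondary endpoint in a 10-subject feasibility study. The primary VAS analysis does not use skin temperature. The change is worth making because it is specific and costs almost nothing.

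**What to change.** **In 4-6-2:** state that the covering state of the measured area is the same before all three thermograms, with both shoulders treated alike. Either leave both uncovered throughout, or cover both for the same time before each image and fix one uncovering interval for all three.

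**If that is not done, in 9-1-3:** rest the skin-temperature conclusion on the before-to-immediate contrast, and report the 15-minute value descriptively with a note that it followed covering.

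**Optional, in 9-1-3:** report the treated-minus-untreated difference at each time, in an area of the same size, from the whole-body thermograms already specified ("Thermography: skin surface temperature of the whole body and the area to be treated"). This should be supportive only, and only with matched covering. Two caveats should be stated: baseline thermography follows one-sided EMG loading, and a systemic effect would be subtracted out.

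The cost is one instruction on covering and one or two sentences of analysis text. No additional thermogram, visit or subject is needed.

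### The 15-minute VAS is rated straight after a fatiguing weight hold and the baseline VAS before any hold, so load is aliased with time in the primary analysis

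*Protocol*

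**What the plan says.** Section 4-6-2 makes its sequence binding: "The position of the patient during the protocol is the sitting position, and the following order is used".

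- **Before treatment.** Rest and vital signs are step 1, and step 2 is "The research subject will fill out the questionnaire (before the procedure". Skin observation is step 3. Step 4 then reads "Measurements will be made in the following order: muscle ultrasonography of both shoulders, surface electromyography, thermography, and pressure pain threshold".
- **Immediately after.** Skin observation, thermography and pressure pain threshold come first, then "The research subject will fill out the questionnaire (immediately after the treatment".
- **At 15 minutes.** Step 1 starts with skin observation and continues "thermography, pressure pain threshold (on the treated side only), muscle ultrasonography, and surface electromyography are measured in this order". Step 2 is "The research subject will fill out a questionnaire (15 minutes after the treatment". The 5-minute rest is step 3.

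The examination methods in the same section describe the EMG as a loading test of muscle fatigue in the trapezius and deltoid: "The load is applied by holding a 2- to 3-kg weight on the treating side". The hold lasts 2 minutes and may be shortened if not tolerated. Ultrasonography of the same muscles is done together with it, at rest and under load.

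The VAS items are shoulder pain and shoulder stiffness. Section 9-1-2 analyses the three VAS ratings by one-way repeated measures ANOVA or Friedman's test as the primary analysis, at p<0.05 (section 9-4). The study is single-arm and uncontrolled. EMG and ultrasonography are exploratory endpoints (section 4-1-3).

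**The concern.** The primary endpoint asks subjects how stiff and painful the shoulder feels. An exploratory test tires the muscles of that region, and it falls at different points relative to the three ratings. A change between ratings can then reflect the hold as well as the irradiation.

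Fatigue would plausibly raise the score. The main risk is therefore that real relief at 15 minutes is understated or lost. The planned test has no direction, so a load-induced rise could also make the time effect significant with no treatment effect at all. No analysis can repair this afterwards: every subject has the same sequence, there is no control arm, and the comparisons with the non-treated side in section 9-1-3 are struck out. The weight (2 to 3 kg) and the duration may vary, so a fixed amount cannot be subtracted.

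**Working it through.** **Step 1: load history at each rating (section 4-6-2).**

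| VAS rating | Weight holds completed before it | Position of the latest hold |
|---|---|---|
| Before treatment | 0 | none |
| Immediately after | 1 | before irradiation, with thermography, pressure testing and irradiation in between |
| 15 minutes after | 2 | the step directly before, with no rest specified |

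The count is 0, 1, 2 in every subject, so load and time are completely aliased.

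**Step 2: inputs for size.** The protocol gives 10 enrolled and about 5 to 7 as the minimum evaluable (section 9-3), three time points, and a 0.05 level taken here as two-sided for the contrast. It gives no power calculation to reproduce, and no VAS SD, expected relief or load effect. The following are assumptions: independent normal errors with within-subject SD of 1; relief of 1.414 SD at both post-treatment times, chosen because it gives the 15-minute contrast 80% power at n = 10; and a load shift d that worsens the 15-minute rating only. The last is a simplification, since the immediate rating also follows a hold.

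**Step 3: planned ANOVA with true relief.** The means are (0, −1.414, −1.414 + d). The noncentrality is λ = n × Σ(mean − grand mean)², referred to F with 2 and 2(n − 1) = 18 df, critical value 3.55.

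**Step 4: 15-minute versus baseline contrast.** This is a paired t with 9 df, critical value 2.26, and noncentrality (1.414 − d) × √10 / √2. The protocol does not plan this test; it shows what happens to the rating most exposed.

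| d (SD) | λ | ANOVA power | t noncentrality | Contrast power |
|---|---|---|---|---|
| 0 | 13.33 | 86% | 3.16 | 80% |
| 0.25 | 11.39 | 80% | 2.60 | 64% |
| 0.5 | 10.28 | 75% | 2.04 | 45% |
| 1.0 | 10.57 | 77% | 0.93 | 13% |

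The ANOVA turns up again at 1.0 SD because it rejects for any difference among the three means, including a rise from the immediate to the 15-minute rating.

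**Step 5: no treatment effect.** The means are (0, 0, d), so λ = n × (2/3) × d².

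| n | d | λ | ANOVA rejects |
|---|---|---|---|
| 10 | 0.5 | 1.67 | 17% |
| 10 | 1.0 | 6.67 | 56% |
| 7 | 0.5 | 1.17 | 13% |
| 7 | 1.0 | 4.67 | 38% |

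Simulation at n = 10 shows the direction. Of the 17% rejections at 0.5 SD, about 16 points have the 15-minute mean highest, and only 0.6 points have it below baseline. At 1.0 SD the split is about 55 points and 0.2 points.

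**Step 6: Friedman alternative.** With the shift expressed as 0.5 between-subject SD, n = 10 and no treatment effect, ANOVA and Friedman reject in 31% and 23% of trials at an assumed correlation of 0.5, and in 66% and 51% at 0.8. With no shift, both stay near 5%. The choice of test does not remove the problem.

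**The case against.** Four points can fairly be made against this.

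1. **The planned test loses little power.** A reader might infer from the contrast figures that the primary analysis collapses to 13%. It does not: section 9-1-2 plans one three-time test, and under the same assumptions that test loses about 6 to 11 points. This stands. It gives limited comfort, though, because a significant result would no longer say which way the 15-minute rating moved or why.
2. **The extra rejections are not false claims of relief.** A reader might take 17% to 56% as the chance of wrongly declaring the device effective. Under the assumed worsening, nearly all of these rejections would show as worsening. This stands.
3. **Attribution is already limited.** A reader might infer that the weight hold is what prevents a causal reading. The single-arm, open-label design does that anyway: placebo response, rest and regression to the mean remain whatever the order. Section 9-3 also calls this a feasibility study. This stands, but section 3 still sets out to verify change against the pre-treatment state, and the load adds an avoidable bias to exactly that comparison.
4. **Moving the baseline to after the first hold could be worse.** It would match the load states in name, but residual fatigue could inflate the baseline, and recovery would then look like relief. The protocol supports no particular rest length that would prevent this. This stands and shapes the fix.

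The load history of the treated shoulder is also less certain than the text suggests. The EMG load is placed on the treating side, yet that side is decided in step 5, after the pre-treatment EMG in step 4.

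**Conclusion.** The defect in order is certain from the text. The baseline VAS is unloaded, the immediate VAS follows one hold, and the 15-minute VAS directly follows a second, with rest only afterwards. Load is aliased with time in the primary analysis and cannot be separated from it.

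The size is not known. It depends on the load shift, the true relief and the within-subject SD, none of which the protocol states. The most plausible harm is masked relief at 15 minutes: modest for the planned overall test, potentially large for the 15-minute change itself. Significance driven by the load alone is possible and would almost always appear as worsening. The protocol does not support the readings that the primary test is ruined, that false relief is likely, or that a new order would establish a device effect. It does support changing the order, because an exploratory measurement is disturbing the primary one for no gain.

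**What to change.** - **15-minute block of section 4-6-2.** Place the VAS questionnaire after skin observation, thermography and pressure pain threshold, as in the immediate block, and before muscle ultrasonography and EMG.
- **Baseline.** Keep the pre-load VAS as the analysis baseline. Optionally add a second VAS directly before irradiation, used only as a sensitivity baseline to show any carry-over from the first hold. Do not replace the baseline with a post-load rating.
- **Treated side.** Reconcile the EMG method, which loads the treating side, with steps 4 and 5 of the pre-treatment block, where that side is chosen only after the EMG.

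The cost is small. The 15-minute EMG starts a minute or two later, and the optional rating adds one short questionnaire to a session of about one hour (section 12-3). The immediate and 15-minute ratings would then both follow one hold. The remaining difference from baseline is that first hold, which the optional rating would make visible.

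### Section 4-6-2 ties the pre-treatment EMG load test to the treating side, but decides that side only after the test

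*Protocol*

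**What the plan says.** The pre-treatment part of Protocol section 4-6-2 is a numbered sequence introduced as the order to be used.

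- Step 3: "Observe the skin at the treatment site".
- Step 4: "Measurements will be made in the following order: muscle ultrasonography of both shoulders, surface electromyography, thermography, and pressure pain threshold".
- Step 5: "The results of the examination are confirmed, and the treating side is decided". The only criterion given is: "The side with the lower pressure sore meter reading is the treatment side".

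The examination and evaluation methods in the same section describe the EMG test by side. Item 5 says "Weight-loading test is performed on the shoulder of the treatment site", then "The load is applied by holding a 2- to 3-kg weight on the treating side", and for the other arm "The arm of the non-treated side should be in a posture to support the upper body". Item 6 repeats the rule: "Measurement of the EMG load is performed on the shoulder on the side to be treated". The entry on muscle ultrasonography has it run at the same time as the EMG examination, both at rest and under load.

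Section 9-1-4 compares the EMG response to loading, and the muscle properties seen on ultrasonography, between the pre-treatment and 15-minute measurements. Sections 4-1-3 and 7-1 list these as the exploratory endpoints.

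**The concern.** The load test is defined by a side, and that side is defined by a measurement taken two items later in the same step. Staff who reach the EMG in step 4 do not yet know which arm should hold the weight and which should support the body. The protocol gives no provisional side and no rule for this situation.

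What is at stake is the treated-side baseline for the 9-1-4 comparisons. By 15 minutes after treatment the side is known, so that test falls on the treated shoulder. If the other shoulder was the one loaded beforehand, the subject has no matching earlier value, and an untreated baseline cannot be obtained after irradiation. The treatment and the EMG and echo measurements are also assigned to different people (section 4-6-1), so an unwritten solution may not be applied in the same way to every subject.

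**Working it through.** The protocol gives no figure to reproduce here. The check is a trace of what each step needs and when that becomes available.

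1. **What the pre-treatment load test needs.** The treating side, for the weight, and the non-treated side, for support (4-6-2 methods, items 5 and 6).
2. **What the treating side needs.** Meter readings from both shoulders, because the criterion is the lower of the two (4-6-2, criterion under step 5).
3. **When those readings exist.** The pressure pain threshold is the fourth and last measurement of step 4. EMG is the second.
4. **Result.** EMG (second) needs the side (step 5), which needs the threshold (fourth). The stated order runs against the dependency.
5. **Ultrasonography.** A resting scan of both shoulders can be done as ordered. The scan under load is tied to the EMG test and has the same problem.
6. **Skin observation in step 3.** It also names the treatment site before there is one, but looking at both shoulders meets it and no analysis depends on it.
7. **Thermography.** Not affected, because the whole body is imaged.

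Staff then have two ways to proceed.

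| Way to proceed | Agreement with the text | Effect on 9-1-4 |
| --- | --- | --- |
| Load both shoulders before treatment | Keeps the step 4 order; departs from items 5 and 6, which load one side and use the other arm as support | No pair lost; loading before treatment rises from up to 2 minutes to 2 × 2 = up to 4 minutes per subject |
| Load one shoulder chosen in advance | Agrees with items 5 and 6 only if that shoulder turns out to have the lower reading | Each subject treated on the other side lacks a treated-side baseline |

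For the second way, let p be the chance that the shoulder chosen in advance is the one later treated. The expected number of subjects without a usable pair is 10 × (1 − p), with 10 the planned enrolment in 4-2-1. The protocol gives no value for p and does not direct this procedure, so the number cannot be determined.

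**The case against.** The strongest reply is that the protocol already implies loading both shoulders. The side criterion compares two readings, so the last item of step 4 must be measured on both sides. The only words in that step that could say so are the reference to both shoulders at the head of the list, and if they reach the last item they plausibly cover EMG as well. The steps after treatment restrict the threshold to the treated side, which fits a pre-treatment block done on both. Ultrasonography of both shoulders, performed together with the EMG and under load, points the same way.

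Much of this stands. It makes loading both shoulders a plausible reading, and under it no data are lost. It does not remove the conflict: the methods text still puts the weight on the treating side and gives the other arm a different task. If loading both was intended, that text needs correcting.

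Three stronger readings are tempting, and the document does not support them.

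- **The test cannot be performed at all.** It can, on both shoulders. What fails is following both parts of the section together.
- **A large share of pairs will be lost.** An assumed p of 0.5 to 0.8 gives 10 × 0.5 = 5 down to 10 × 0.2 = 2 subjects without a pair. These figures describe a one-shoulder workaround that no text directs. The approximate minimum of 5 to 7 in section 9-3 refers to the endpoints in general and is not a threshold for EMG pairs.
- **Loading both shoulders would damage the pressure pain threshold endpoint.** The treated shoulder is meant to be loaded before its baseline threshold anyway, and thermography comes in between. The added test loads the other shoulder, whose threshold serves only to choose the side; current section 9-1-3 analyses the treated side alone.

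**Conclusion.** Section 4-6-2 contradicts itself in current text. The pre-treatment load test, and the ultrasonography done during it, are assigned to a side that the stated sequence has not yet determined. This rests on taking the order of steps 4 and 5 as binding, as the section says, and on the methods text applying to the pre-treatment test as well as the 15-minute one.

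The issue is minor. It reaches only the exploratory EMG and loaded-ultrasound comparisons in a single-arm feasibility study of 10 subjects. The primary VAS endpoint is not affected, and no effect on a secondary endpoint or on safety has been shown. The loss ranges from none, if both shoulders are loaded, to an unknown number of baselines, if one is chosen in advance. It still merits correction, because a missing treated-side baseline cannot be recovered and the repair is small.

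**What to change.** Either of two changes to section 4-6-2 is enough.

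1. **Decide the side first.** Take a meter reading on both shoulders and decide the treating side before step 4; placing this between steps 2 and 3 also settles the skin observation. Then run step 4 in its present order, with the baseline pressure pain threshold still measured at its end, and remove the side decision from step 5. State that the side stays as decided even if the later reading ranks the shoulders differently. The methods text can then be followed unchanged. Cost: two presses on each of two shoulders, 2 × 2 = 4 extra presses per subject, at the site where the baseline threshold is measured later.
2. **Write in loading of both shoulders.** Amend items 5 and 6 so that before treatment both shoulders are load-tested in a fixed order, with the arm not under test supporting the body, and state in 9-1-4 that the treated side is used. Cost: one extra load test of about 2 minutes per subject.

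Neither needs new equipment or staff.
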